## Methods

### Study Design

This UCF intervention was a parallel group, 2-arm, pragmatic waitlist randomized trial with 1:1 allocation ratio to either intervention or waitlist control. The intervention group completed the first 24-week UCF program, followed by a 24-week observation period. The control arm served as a waitlist group, receiving no intervention during the initial 24 weeks but undergoing the same intervention in the following 24 weeks after the intervention group completed. Participants in both arms completed assessment at baseline, 6-month, and 12-month follow-up. We reported using the standard protocol items: recommendation for interventional trials (Standard Protocol Items: Recommendations for Interventional Trials [SPIRIT]) checklist (Checklist 1) [29].

### UCF Intervention

The UCF intervention was designed as a structured 24-week care farming curriculum and delivered by certified horticulturists and trained farmers. It was intended to engage older adults with the natural environment through therapeutic farming (eg, nature walks around sensory gardens and reflecting on nature landscape) and gardening activities (eg, plant cultivation and gardening) in green spaces, with the goal of enhancing QOL across physical, psychological, and social domains of health. Both the intervention and waitlist control arms participated in a weekly UCF program, lasting between 2.5 and 3 hours per session over 24 weeks. The program included activities such as fertilization, sowing, watering, transplanting, maintaining, and harvesting vegetables and herbs. The UCF intervention included structured, facilitated sessions involving a range of agricultural and food-growing activities, such as seedling propagation, composting, harvesting of edible greens, and hands-on food preparation using farm-grown produce. These went beyond casual gardening and were intentionally designed to promote physical activity, encourage teamwork and autonomy, and stimulate cognitive and sensory engagement. Each participant selected 1 weekday to attend weekly. All sessions offered each week were identical in content. For example, group 1 attended a Monday session for 24 weeks. This arrangement was necessary as the intervention site could not accommodate all 60-70 participants, depending on the study arm. Furthermore, smaller group sizes promoted meaningful discussion and the forming of social networks. Treatment adherence was monitored using attendance sheets. Additionally, treatment fidelity was used to monitor and ensure the consistency of intervention content delivery.

Trainers facilitated the 24-week UCF intervention, engaging them with horticultural and urban care farming activities to acquire relevant skills and knowledge. To ensure consistent content and activities delivery, trainers were provided training materials, which listed the objectives and activities (Supplementary 1 in Multimedia Appendix 1). Participants received guidance on fundamental planting techniques, information on different varieties of plants, and their nutritional value. UCF-integrated activities related to gardening and farming that fostered social connections and promoted psycho-emotional well-being were also included in the intervention. Additionally, participants gained insights into the benefits of naturally grown food without chemical additives and were encouraged to make healthier dietary choices. This intervention included other activities such as cooking, nutrition, and arts and crafts. Table 1 presents the overview of the activities that participants engaged in the intervention.

A small incentive of S$10 (US$7.35) [30] per session was reimbursed to participants to cover travel costs to the intervention site. Participants were given vegetable packs fortnightly in addition to crops they had personally cultivated. This hands-on experience provided farm-to-table experience. The practice also encouraged participants to reflect on the quality of their produce.

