8 sessions	These 8 sessions were held at the community garden near the national garden. Care farming activities involved participants working collaboratively to plan, carry out, and care for crops from initial germination through to harvest in the community garden. Participants also prepared meals together using the produce they planted and harvested.	15 minutes of briefing of daily activities 120 minutes of gardening and horticultural activities with short breaks in between 15 minutes of debriefing	Increase physical activity Improve physical performance Strengthen working memory Gain a sense of achievement Care for plants—promote sense of purpose and meaningfulness Improve gross and fine motor skills Improve community engagement and social interaction
1 session	Participants organized a collective indoor community event to showcase their harvest and promote community gardening activities. Participants from different session days came together to attend this event. Trainers assisted participants in preparing for the community event.	150 minutes of preparation, sharing, and exchange among participants and urban farming experts and horticulturists	Improve place attachment Improve community engagement and social interaction

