### Sample Size

This study aimed to compare the QOL between the treatment and waitlist control participants, using a 1:1 allocation ratio. Based on a prior study of the overall WHOQOL measure, if the true difference-in-differences estimate between experimental and control means is 4.93 with a standard deviation of 9.29 [46], a sample of 57 intervention and 57 control subjects is required to reject the null hypothesis based on a 2-tailed significance level of 5% and power of 80%. We inflated the sample by 20% to account for dropouts and the potential loss of participants due to noncompliance and faulty measurements. Accounting for all these factors, the total sample size required for 2 arms is 138 participants.

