#### Statistical Analysis

The primary analysis, intention-to-treat, will be conducted using a linear mixed effects model with overall WHOQOL score as the dependent variable and the interaction effect of intervention allocation and time as the independent variable. Domain-specific scores will also be analyzed. To address potential bias arising from missing data due to attrition or incomplete responses, our primary longitudinal analyses will employ linear mixed-effects models, which are robust to unbalanced data structures and can handle missing observations under the missing-at-random assumption. While listwise deletion may be used for cross-sectional comparisons or descriptive analyses, this will be clearly indicated. Secondary outcomes will be analyzed using similar methods. These analyses will be conducted at 6-month follow-up to investigate the effectiveness of the intervention as well as post-intervention behavioral maintenance at 12 months. Sensitivity analysis using the per-protocol approach will also be carried out. Baseline characteristics of participants who discontinued or were lost to follow-up will be compared to those who completed the study to investigate differential dropout between intervention and control groups.

Due to potential imbalances between the groups, further analysis techniques, such as adjustment or matching of baseline characteristics, will be used in the difference-in-difference analysis. Specifically, we will adjust or match on key baseline covariates (eg, age, gender, years of education, marital status, and housing type) to improve group comparability at baseline in case of any imbalance despite randomization. This approach improves covariate balance and enhances the comparability of groups prior to applying linear mixed models for outcome analyses. Conducting both intention-to-treat and per-protocol analyses for this behavioral intervention allowed comparison of the results and provided a comprehensive understanding of the treatment effect. All evaluations were and will be performed using a 2-sided test at the 5% level of significance.

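### The intervention runs in fixed weekday groups, but the sample size assumes independent participants and the described analysis names no group-level correlation

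*Protocol article*

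**What the plan says.** **Delivery.** The UCF Intervention section says "Each participant selected 1 weekday to attend weekly", and illustrates it: "For example, group 1 attended a Monday session for 24 weeks". It gives a therapeutic reason for the arrangement as well as a logistic one: "smaller group sizes promoted meaningful discussion and the forming of social networks". Table 1 describes eight community-garden sessions of joint work: "Care farming activities involved participants working collaboratively to plan, carry out, and care for crops from initial germination through to harvest". The Study Design section gives the waitlist arm no intervention during the first 24 weeks.

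**Sample size.** The Sample Size section starts from "if the true difference-in-differences estimate between experimental and control means is 4.93 with a standard deviation of 9.29" and concludes that "a sample of 57 intervention and 57 control subjects is required to reject the null hypothesis". It then adds 20%, which it assigns to dropout, noncompliance and faulty measurements, for a total of 138.

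**Analysis.** The Statistical Analysis section specifies a "linear mixed effects model with overall WHOQOL score as the dependent variable", with the allocation-by-time interaction as the effect of interest. It names no term for session group or trainer. The limitations paragraph of the Discussion says the approach deals with within-subject correlation. It also mentions robust standard errors, without saying at what level they are clustered.

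**The concern.** People who spend 24 weeks in the same small group, gardening and cooking together and forming social ties, may come to change alike. The Introduction expects this kind of collective activity to improve the psychological and social domains, which are part of the primary score. Up to 6 months the waitlist arm has no such groups, so the primary contrast is partially nested: clustered in one arm and independent in the other.

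If change in WHOQOL is correlated within groups, the mean of the intervention arm varies more than independent observations would. A model without that component gives too small a standard error for the primary effect, too narrow an interval, and a nominal 5% test that rejects too often. The planned number of participants then also gives less than the stated power.

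**Working it through.** **Inputs from the Sample Size and Results sections.** Difference 4.93, SD 9.29, two-sided 5%, 57 per arm; enrolled 67 + 70.

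**Assumptions, because the article gives neither.** Five weekday groups (3 to 6 also tried), and ICC of change in WHOQOL from 0.01 to 0.10.

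**1. The plan's own figure.** Normal approximation: n = 2 × (9.29 × (1.960 + 0.842) / 4.93)² = 55.74, so 56 per arm. With the noncentral t distribution, power is 79.5% at 56 and 80.2% at 57. The stated 57 is therefore the independent two-sample t-test figure. Inflation: 57 × 1.2 = 68.4, rounded up to 69, and 2 × 69 = 138. Nothing is left over for a design effect.

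**2. Standard error with groups in one arm.** Group size m = 57/5 = 11.4. Design effect in the intervention arm: DE = 1 + (m − 1) × ICC. Standard error: SE = 9.29 × √(DE/57 + 1/57). Under independence SE = 9.29 × √(2/57) = 1.740. At ICC 0.05, DE = 1 + 10.4 × 0.05 = 1.52 and SE = 9.29 × √(2.52/57) = 1.953, a ratio of 1.122.

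**3. Type I error if groups are ignored.** 2 × [1 − Φ(1.96 / ratio)]. At ICC 0.05: 1.96/1.122 = 1.747, giving 8.1%.

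**4. Power.** Noncentral t with noncentrality 4.93/SE, first with 112 df, then with Satterthwaite df = (DE + 1)² / (DE²/4 + 1/56). At ICC 0.05 the df are 6.350/0.5955 = 10.7.

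Results for 57 + 57 and 5 groups:

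| ICC | DE | SE | SE ratio | Type I error, groups ignored | Power, 112 df | Satterthwaite df | Power, Satterthwaite |
|---|---|---|---|---|---|---|---|
| 0.01 | 1.10 | 1.785 | 1.026 | 5.6% | 78.2% | 13.7 | 72.7% |
| 0.02 | 1.21 | 1.828 | 1.051 | 6.2% | 76.2% | 12.7 | 70.2% |
| 0.05 | 1.52 | 1.953 | 1.122 | 8.1% | 70.6% | 10.7 | 63.0% |
| 0.10 | 2.04 | 2.145 | 1.233 | 11.2% | 62.5% | 8.7 | 53.3% |

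**5. Number of groups.** At ICC 0.05 with 3, 4, 5 or 6 groups, power (112 df) is 64.5%, 68.2%, 70.6% or 72.3%.

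**6. Everyone enrolled is analysed.** With 67 + 70 and no loss, m = 67/5 = 13.4 and SE = 9.29 × √(DE/67 + 1/70). With 135 df, power is 86.9% under independence, and 84.8%, 82.8%, 76.6% and 67.4% at ICC 0.01, 0.02, 0.05 and 0.10. The Satterthwaite formula on the same inputs gives 79.6%, 76.6%, 68.4% and 57.0%.

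**The case against.** **The model is condensed.** The Statistical Analysis section lists no random effects at all, and a fuller specification may sit in an analysis plan that is not shown. This is fair, so it cannot be said that the final model omits groups. But the article does say which dependence its approach handles, and group dependence is not mentioned. An unseen plan also could not alter the published sample size calculation.

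**Robust standard errors.** A reader might infer that these cannot cover session groups. The article does not support that, because the clustering level is not stated. Clustered on participant they would not help; clustered on about five groups they would be unreliable.

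**Certainty.** A reader might infer that the interval is too narrow as a matter of fact. That needs a positive ICC in change, and no ICC is given. At 0.01 the type I error is only 5.6%.

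**Mechanism.** Free choice of weekday is not the problem. Participants were individually randomised, and sorting by day preference alone leaves the test at about 5%. Nor are shared trainers established, since no passage assigns trainers to days. Identical weekly content, the facilitator manual and the fidelity checks may reduce differences in delivery. They do not remove peer effects, which are what the point rests on.

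**The buffer.** Enrolment exceeded 57 per arm, and at a small ICC the surplus can absorb the loss if few drop out. With about 10% loss (60 + 63, an assumption), the same formulas with 121 df give 81%, 79% and 73% at ICC 0.01, 0.02 and 0.05.

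**Conclusion.** The point holds in conditional form. The sample size is firmly an independent-participants figure, in a trial whose intervention is delivered through persistent groups meant to influence the outcome. The described analysis names only within-subject correlation. If the ICC of WHOQOL change is positive and groups are left out of the model, the primary standard error is too small. The 80% power at 57 per arm is then not delivered.

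The size depends on two assumed quantities. With 5 groups and ICC 0.01 to 0.10, type I error is about 5.6% to 11%. Power at 57 + 57 is about 78% to 63%, or 73% to 53% with degrees of freedom that respect the number of groups. With all 67 + 70 analysed it is about 85% to 67% before that correction, so the dropout buffer covers only a small ICC with little loss.

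The one-arm clustering describes the 6-month contrast only; by 12 months the waitlist arm has also been through weekday groups. The article reports that the baseline and 6-month analysis is still under way, so the model can still be settled.

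**What to change.** - **6-month contrast, primary and secondary outcomes.** Fit a partially nested model: a random effect for weekday group in the intervention arm, each waitlist participant as a singleton, and Satterthwaite or Kenward-Roger degrees of freedom. Keep the group term whatever its estimate, and report the ICC.
- **12-month analysis.** Use each arm's own weekday groups; the singleton structure no longer applies to the waitlist arm.
- **Group assignment.** State a rule for intention-to-treat participants who never attended, since attendance sheets may not place them in a group.
- **Robust standard errors.** State the clustering level.
- **Power.** State the number of groups, and say that 80% holds only under independence. Give a range over ICC computed with the same degrees of freedom as the analysis. With 5 groups, 57 + 57 and Satterthwaite df, that range is 73% to 53% for ICC 0.01 to 0.10.

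No new data collection should be needed, provided that group membership can be recovered from the attendance sheets. The price is a wider interval and a group variance estimated imprecisely from few groups. Restating the power cannot change a completed enrolment, but it tells readers how to weigh a null result.

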### Study Setting

The study was held in the western region of Singapore, at a national garden equipped with growing edibles and therapeutic gardens, and a rooftop community garden. Enrolled participants began the intervention at the national garden, which includes foundational knowledge and hands-on training on plants and farming. As part of the intervention, they transitioned to a community rooftop garden, collaborating to grow, maintain, and harvest plants.

The UCF intervention was designed as a structured 24-week care farming curriculum and delivered by certified horticulturists and trained farmers. It was intended to engage older adults with the natural environment through therapeutic farming (eg, nature walks around sensory gardens and reflecting on nature landscape) and gardening activities (eg, plant cultivation and gardening) in green spaces, with the goal of enhancing QOL across physical, psychological, and social domains of health. Both the intervention and waitlist control arms participated in a weekly UCF program, lasting between 2.5 and 3 hours per session over 24 weeks. The program included activities such as fertilization, sowing, watering, transplanting, maintaining, and harvesting vegetables and herbs. The UCF intervention included structured, facilitated sessions involving a range of agricultural and food-growing activities, such as seedling propagation, composting, harvesting of edible greens, and hands-on food preparation using farm-grown produce. These went beyond casual gardening and were intentionally designed to promote physical activity, encourage teamwork and autonomy, and stimulate cognitive and sensory engagement. Each participant selected 1 weekday to attend weekly. All sessions offered each week were identical in content. For example, group 1 attended a Monday session for 24 weeks. This arrangement was necessary as the intervention site could not accommodate all 60-70 participants, depending on the study arm. Furthermore, smaller group sizes promoted meaningful discussion and the forming of social networks. Treatment adherence was monitored using attendance sheets. Additionally, treatment fidelity was used to monitor and ensure the consistency of intervention content delivery.

### Inclusion and Exclusion Criteria

Participants who enrolled in the study met these inclusion criteria: (1) aged 50 and 85 years, (2) willing to take part in either the intervention or waitlist control arm, (3) agree for their data to be used for research purposes, and (4) ambulant to be able to carry out gardening tasks (eg, watering the plants). Participants were excluded if they had medical conditions that could compromise or interfere with their ability to participate, upper or lower disabilities that limit their mobility, or were unwilling to provide their medical or health records for research.

### Ethical Considerations

The study has been approved by the National University of Singapore Institutional Review Board (NUS-IRB-2023‐191). The approval has also been granted for the pilot study of this project. Any modification to the approved protocol will be submitted for review by the ethics committee. If there are any amendments, changes will be reflected in the trial registry. All participants provided written consent prior to the participation. Data collected was anonymized and kept confidential. Consent from participants was obtained to publish the results from deidentified data. To acknowledge the time and effort required, participants were provided with a S$30 (US $22.05) [30] honorarium for each data collection session (approximately 210 min). The amount was set at a level appropriate to compensate participants without constituting undue inducement, consistent with ethical guidelines for research involving human participants. Participants’ data (eg, case record forms, laboratory tests, information sheets, and consents) are stored in a locked cabinet in a researcher’s office. All other data (eg, biomarker results, and responses to surveys) have been deidentified. All personal identifier data (eg, names and contact information) are kept separate from the research data by a trusted third party. All data collection has been completed, and a link (otherwise known as code key) was passed to the trusted third party so the research team only works with deidentified data. After the study has been completed, all personal data will be kept for a maximum of 5 years. Research and biological data will be kept for a maximum of 10 years. During the study, the data will only be accessible to the research team. The research team has exclusive rights to the deidentified data for 36 months after the trial is completed.

### Dissemination

In addition to disseminating our research findings to the funder of this study, we will disseminate our findings to other countries, the study participants, and the research community. We will also follow the authorship guidelines of the International Committee of Medical Journal Editing (ICMJE) [31].

**Table 1. T1:** Summary of indoor and outdoor care farming activities across the 24-week intervention.

No. of sessions	Program description	Activity breakdown	Goals of intervention
15 sessions	Participants engaged in indoor plant- and farming or gardening-related knowledge-sharing sessions led by trained horticulturist farmers. Participants learned basic skills and knowledge in maintaining a garden and acquired skills in pruning, soil mixing, transplanting, and composting, as well as knowledge of the properties of plants and vegetables. Example topics included composting, the properties and nutritional value of plants and vegetables, and gardening techniques. A few indoor sessions also included microgreen planting, which participants brought home to tend to, as well as nature-art activities designed to foster creative expression and social interaction. Following the indoor activities, participants attended outdoor hands-on sessions where they engaged in green maintenance in the designated garden or farm area and practiced the gardening techniques introduced during the indoor sessions. Several outdoor sessions included therapeutic walks, during which participants took part in guided educational strolls through therapeutic gardens to learn about the unique properties of local plants and to strengthen their connection with nature. During these walks, participants engaged in sensory-based activities involving touch, scent, and visual observation, which created opportunities to reconnect with local flora and fauna and to reminisce. Several of the 15 sessions at the national garden focused on nutrition, cooking, and consumption of herbs, vegetables, and fruits. Participants learned about the nutritional value and importance of consuming more plant-based diets. Live cooking demonstrations were provided, and participants sampled the cooked vegetables. Participants were encouraged to share their recipes to promote greater social interaction.	Indoor and outdoor activities: 20 minutes of briefing of daily activities 60 minutes of indoor gardening and sharing of farming tips 60 minutes of outdoor gardening activities with short breaks in between 10 minutes of debriefing Nutrition and cooking activities: 20 minutes of briefing of daily activities 50 minutes of gardening, harvesting, and preparation 60 minutes of cooking and demonstration, food sharing, and social interaction 20 minutes of debriefing	Increase physical activity Improve gross and fine motor skills Strengthen working memory Gain a sense of achievement Care for plants—promote sense of purpose, meaningfulness, and hope Improve nutrition knowledge and attitude toward vegetable consumption Improve interpersonal interaction
8 sessions	These 8 sessions were held at the community garden near the national garden. Care farming activities involved participants working collaboratively to plan, carry out, and care for crops from initial germination through to harvest in the community garden. Participants also prepared meals together using the produce they planted and harvested.	15 minutes of briefing of daily activities 120 minutes of gardening and horticultural activities with short breaks in between 15 minutes of debriefing	Increase physical activity Improve physical performance Strengthen working memory Gain a sense of achievement Care for plants—promote sense of purpose and meaningfulness Improve gross and fine motor skills Improve community engagement and social interaction
1 session	Participants organized a collective indoor community event to showcase their harvest and promote community gardening activities. Participants from different session days came together to attend this event. Trainers assisted participants in preparing for the community event.	150 minutes of preparation, sharing, and exchange among participants and urban farming experts and horticulturists	Improve place attachment Improve community engagement and social interaction

